### Dietary intake and physical activity assessment

In order to ensure lack of change in dietary intakes of participants during the study, we will collect dietary intake data through the use of a 24-h dietary recall every three weeks throughout the study. These dietary recalls will be distributed through the week days to cover two working days and two weekends. Due to COVID-19 pandemic, dietary recalls will be completed through phone calls, not by face-to-face method. In these phone calls, participants will be asked to report their dietary intakes in a preceding day based on household measures. All reported foods in these recalls will then be converted to grams using available booklets. The average intake based on four dietary recalls will be considered in the analysis.

Participants will be asked not to change their physical activity during the trial. To make sure about this, we will request study subjects to record their physical activity in four separate days throughout the study including two working days and two weekends. All participants will be instructed how to record the type, intensity and time spent in each activity in a certain form that will be given to them at the study baseline. In order to process the physical activity records, we will use earlier published guidelines about MET-h/day values for each type of physical activity, in which we will consider the time spent for a certain physical activity by each participant. All records would be reviewed immediately to find possible errors and the problems will be resolved by interview.

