### Statistical analysis

In this study, all analyses will be done using SPSS software version 26. Normal distribution of data will be assessed by the application of Kolmogorov–Smirnov test. In case of a non-normal distribution, we will apply logarithmic transformation. Results will be reported as mean ± standard deviations (SD) or medians (interquartile ranges). General characteristics and dietary intake of individuals between the two groups will be compared using independent t-test and chi-square test as needed. Repeated measure analysis of variance (RM-ANOVA) will be used to examine the effects of probiotic yogurt consumption on outcome variables, where we will examine the effects of time, intervention as well as time-group interaction effects. In this analysis, baseline values of outcome variables will be controlled for. We will also perform post hoc tests after ANOVA analysis to examine the variables between study groups. In case of any difference between the two groups in terms of dietary intakes (other than the intervention) and physical activity throughout the study, these differences will be adjusted for in the analysis to reach an independent effect of intervention on study outcomes. Statistical significance will be set to 0.05.

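### The outcome model is to be adjusted for diet and activity measured after randomisation whenever the arms differ; if the yogurt affects either, the result is no longer the effect of assignment.

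*Protocol article*

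**What the plan says.** The rule is in the Statistical analysis section of the protocol article. Its condition reads "In case of any difference between the two groups in terms of dietary intakes (other than the intervention) and physical activity throughout the study", and its action is that "these differences will be adjusted for in the analysis to reach an independent effect of intervention on study outcomes". The same section says "General characteristics and dietary intake of individuals between the two groups will be compared using independent t-test and chi-square test as needed", but it does not name that comparison as the trigger. It gives no threshold, list of nutrients or activity measure.

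The section on dietary intake and physical activity fixes the timing. For diet, "we will collect dietary intake data through the use of a 24-h dietary recall every three weeks throughout the study", and "The average intake based on four dietary recalls will be considered in the analysis". Participants will also "record their physical activity in four separate days throughout the study including two working days and two weekends". Both sets of measurements therefore come from the treatment period. Diet and activity are also recorded in the run-in, but the adjustment rule refers to differences during the trial.

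The main model is a repeated-measures ANOVA with group, time and their interaction, controlling for the baseline outcome. Control for the baseline outcome is a separate matter and is not at issue here.

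**The concern.** In a randomised comparison, an arm difference in diet or activity that appears after the start is either chance or a consequence of assignment, including through differential dropout or reporting. If it is chance, randomisation already accounts for it. If it follows from the yogurt, for example through appetite or displacement of other foods, two things can go wrong.

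- **Lost effect.** Holding the covariate fixed removes whatever part of the benefit passes through it.
- **Spurious effect.** If something unmeasured, such as health consciousness, drives both the covariate and the outcome, conditioning on the covariate links arm to outcome through that factor, even when the yogurt does nothing to the outcome.

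The trial's stated aim is the effect of consuming probiotic yogurt on enzymes, steatosis and fibrosis. Once the rule fires on a real diet change, the result no longer estimates that. The condition is also so open that the covariate set has to be chosen after the data are seen.

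**Working it through.** **Inputs from the article (Participants section).** Type I error 5%, power 80%, 28 evaluable per arm, mean difference 2 in CAP. No SD is given and sidedness is not stated; two-sided is assumed.

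**Effect size implied by 28 per arm.** By the normal formula, SD = 2 × √(28/2) / (1.960 + 0.842) = 2.67, so the standardised effect is 2/2.67 = 0.75. With the noncentral t it is 0.76. Both are back-solved and are not figures in the plan.

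**Assumptions not in the article.** One standardised covariate M, a trigger at p<0.05 on a t-test of M between arms, and the path sizes below. With arm T (0 or 1) and unmeasured factor U:

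- M = a·T + u·U + √(1−u²)·error
- Y = direct·T + b·M + u·U + error

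Effects are in units of the SD of the outcome's own error term. There were 28 per arm and 10,000 runs per scenario, analysed by least squares.

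**1. Mediated effect (total 0.75, a = 0.75, u = 0).** Always adjusting leaves total − a·b.

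- Half mediated, b = 0.5: 0.75 − 0.375 = 0.375.
- 30% mediated, b = 0.3: 0.75 − 0.225 = 0.525.

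The conditional rule fires in about 78–79% of runs, so it falls a little short of full adjustment:

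| Mediated share | Unadjusted estimate (power) | Conditional rule (power) |
|---|---|---|
| 50% | 0.74 (69%) | 0.41 (28%) |
| 30% | 0.75 (75%) | 0.55 (47%) |

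Unadjusted power is below 80% partly because M adds outcome variance: with b = 0.5 the SD is √1.25, so the standardised effect is 0.67.

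**2. No effect on the outcome, shared cause (total 0, a = 0.75, b = 0, u = 0.6).** Given arm, the slope of Y on M is u² = 0.36, so full adjustment gives a bias of −0.36 × 0.75 = −0.27. The conditional rule gives −0.24, with type I error 11.5% against 5.2% unadjusted.

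**3. Arm does not affect the covariate (a = 0).** With one covariate or five, the conditional rule gives no bias and type I error of 4.5% and 4.3%. Across further runs with 1, 5 or 10 covariates the range was 3.9% to 5.6%.

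**4. How often chance alone fires the rule.** For k independent covariates tested at 0.05 this is 1 − 0.95^k: 5% for 1, 10% for 2, 23% for 5 and 40% for 10. Step 3 shows that in this setting a fixed trigger does little damage, so these figures say how often the model changes, not how much harm follows.

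**The case against.** The strongest defence is that the harmful route is unlikely here. Both arms eat 300 g/d of yogurt with the same appearance, packaging and taste. Participants and staff are blinded, and participants are asked to keep their habits. The recalls are there to confirm that intake stays stable, and the rule excludes the yogurt itself. Nothing in the article suggests that the probiotic changes the rest of the diet or activity, still less that it carries 30% or 50% of the effect. All of this stands. It lowers the probability of harm but does not repair the rule, which acts fully in exactly the case where diet does shift.

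A reader might also infer that a data-driven trigger by itself breaks the 5% error rate. The check does not support that: when the arm leaves the covariates alone, type I error stays near 5% and the estimate is unbiased. Inflation needs a real arm effect on the covariate together with a shared cause, or a discretionary choice of covariates, which was not quantified. Nor should the 23% and 40% chances of triggering be read as error rates. The section mentions no confidence interval, so no claim is made about one.

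Finally, one might leave the matter to an analysis plan that is not shown. That would excuse an omission, but the article states the rule outright.

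**Conclusion.** The point holds in conditional form. As written, the plan adjusts for post-randomisation variables when the arms differ, presents the result as the intervention's own effect, and does not say that an unadjusted analysis remains the main one. If the yogurt changes intake or activity, this alters the question and can bias the answer in either direction. If it does not, adjustment triggered by chance under a fixed rule is close to harmless, and what remains is a covariate set not fixed in advance. The 5% error rate can be invalidated but need not be.

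The sizes shown (0.74 to 0.41, 0.75 to 0.55, type I error 11.5%) are illustrations. They rest on an effect size guided by a back-solved value, since the article gives no SD, and on assumed path sizes, a single covariate and a 0.05 trigger, none of which is in the article. Confidence is high that the rule is unsound and low about how much it would matter in this trial. It should be changed.

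**What to change.** - Delete the conditional adjustment from the main analysis.
- State one main model, fixed before the data are seen, with baseline covariates only: baseline value of the outcome, age, sex and BMI. The last three already define the randomisation blocks.
- Report in-trial diet and physical activity by arm descriptively.
- Keep a model adjusted for intake and activity only as a labelled sensitivity analysis, with its covariates named in advance and a note that it does not estimate the effect of assignment.

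The cost is a change of wording. All the data are already to be collected, and the sample size is unaffected.

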**Discussion:**

Probiotics have been suggested as a new strategy in the management of NAFLD. Their effects might be mediated through intestinal microbiota modification and production of short-chain fatty acids. Consumption of probiotic-enriched foods, rather than their supplements, might be a cost-effective method for long-term use in these patients. In case of finding the beneficial effects of probiotic yogurt consumption in the current clinical trial, its inclusion in the dietary plan of NAFLD patients can be recommended.

*Trial registration* This clinical trial was registered in Iranian Registry of Clinical Trials (www.irct.ir) at 2021-04-19 with code number of IRCT20210201050210N1.

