## Patients and methods

### Participants

This study will be a parallel randomized clinical trial (CRT) that will be conducted in Tehran, Iran, in 2021. The sample size was calculated by considering the type 1 error of 5%, the study power of 80% and the hepatic steatosis levels [30] (based on CAP) as a key variable based on data from previous studies. Considering the mean difference in hepatic steatosis levels of 2 dB/mL between the two groups [12], using the suggested formula for parallel clinical trials, we will need 28 patients in each group. However, by taking a possible drop-out of 20% into account, we will recruit 34 patients in each group based on the study inclusion criteria. Outpatients with NAFLD will be recruited from private clinics in Tehran, Iran. The diagnosis of NAFLD will be done by a gastroenterologist based on examination with a fiberoscan. The study is ethically approved by the Bioethics Committee of Tehran University of Medical Sciences, Tehran, Iran, and is registered in the Iranian Registry of Clinical Trials website (http://www.irct.ir).

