### Outcomes

The outcomes of the present clinical trial would be assessment of steatosis, fibrosis, serum liver enzyme levels including aspartate aminotransferase (AST), alanine aminotransferase (ALT), alkaline phosphatase (ALP), Gamma-glutamyl transferase (GGT). Systolic (SBP) and diastolic blood pressure (DBP), lipid profiles including high-density lipoprotein cholesterol (HDL-C), low-density lipoprotein cholesterol (LDL-C), total cholesterol (TC), serum triglycerides (TG) fasting blood sugar (FBS), fasting insulin and glucose hemostasis will also be considered. Weight and BMI will also be assessed. All these measurements will be assessed at study baseline and the end of trial.

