### Glucose homeostasis assessment

Homeostatic Model Assessment of Insulin Resistance (HOMA) and Quantitative Insulin Sensitivity Check Index (QUICKI) will be calculated based on suggested formulas [33, 34]

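### About 18 outcomes are listed with none named primary, the level is 0.05 without a hierarchy, and the recommendation rests on no named outcome: the chance of at least one spurious favourable result is up to about 37%, against 2.5% for one primary test

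*Protocol article*

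**What the plan says.** All places are in the protocol article.

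- **Outcomes.** The list opens with "The outcomes of the present clinical trial would be assessment of steatosis, fibrosis, serum liver enzyme levels" and names AST, ALT, ALP and GGT. Blood pressure and lipids follow, then fasting glucose, and the sentence ends "fasting insulin and glucose hemostasis will also be considered". The section then adds "Weight and BMI will also be assessed". No variable is called primary or secondary.
- **Glucose homeostasis assessment.** Glucose homeostasis becomes two variables: "Homeostatic Model Assessment of Insulin Resistance (HOMA) and Quantitative Insulin Sensitivity Check Index (QUICKI) will be calculated".
- **Participants.** The sample size uses "type 1 error of 5%, the study power of 80" per cent, with steatosis "based on CAP) as a key variable based on data from previous studies". This is the only place where one outcome is singled out.
- **Statistical analysis.** Repeated-measures ANOVA is applied to the outcome variables, with time, group and time-by-group effects examined and post hoc tests added. The level is given as "Statistical significance will be set to 0.05". No order of testing and no adjustment is stated.
- **Abstract, Discussion paragraph.** The recommendation is introduced by "In case of finding the beneficial effects of probiotic yogurt consumption in the current clinical trial", with no outcome named. The main Discussion section has a parallel sentence that also names none.

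**The concern.** A reader cannot tell from this text what would count as success. Suppose CAP shows no difference and ALT or LDL-C does. Nothing stated prevents the trial from being reported as showing a benefit, and the recommendation would then rest on whichever outcome happened to cross 0.05. The 5% type 1 error used for the sample size applies to one test of CAP. It does not describe the error rate of a conclusion that may draw on any of some 18 tests.

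**Working it through.** **The plan's own figures.** The article states no trial-wide error rate, so there is none to reproduce. It does state 28 patients per group for a CAP difference of 2 at 5% and 80%. No SD is given. Taking the test as two-sided, 28 per group implies SD = 2 × √(28/2) / (1.960 + 0.842) = 2.67. The stated 34 per group equals 28 × 1.2 = 33.6, rounded up. These figures confirm that the trial is sized on CAP alone.

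**Count of outcomes.**
- Liver: steatosis, fibrosis, AST, ALT, ALP, GGT = 6
- Blood pressure: SBP, DBP = 2
- Lipids: HDL-C, LDL-C, TC, TG = 4
- Glucose: fasting glucose, insulin, HOMA-IR, QUICKI = 4
- Weight and BMI = 2

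The total is 18. It is 17 if glucose homeostasis counts once, and 19 if waist circumference (measured, but absent from the Outcomes section) is added.

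**Error rates with independent outcomes.** Assume no true effect on any outcome and one two-sided group test each. A significant result in either direction has probability 0.05 per test; a favourable one has 0.025.

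| Number of tests | Either direction, 1 − 0.95^k | Favourable only, 1 − 0.975^k |
|---|---|---|
| 1 (single primary) | 5.0% | 2.5% |
| 6 (liver outcomes in the aim) | 26.5% | 14.1% |
| 17 | 58.2% | 35.0% |
| 18 | 60.3% | 36.6% |
| 19 | 62.3% | 38.2% |

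**Error rates with correlated outcomes.** The documents give no correlations, so these are assumptions. Each line comes from 400,000 simulated sets of 18 normal test statistics with no true effect and critical value 1.96. Outcomes are coded so that a positive value is a benefit.

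| Common correlation | Either direction | Favourable only |
|---|---|---|
| 0.1 | 59% | 33% |
| 0.3 | 51% | 26% |
| 0.5 | 40% | 20% |
| 0.7 | 28% | 14% |
| 0.8 | 22% | 11% |

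A second pattern sets high correlations for near-duplicates (weight with BMI, TC with LDL-C, insulin with HOMA-IR and QUICKI, AST with ALT), moderate ones for some other related pairs, and a background correlation of 0 to 0.3 elsewhere. It gives 45–52% in either direction and 23–30% favourable.

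**Comparison.** Against 2.5% for one primary test, 36.6% is about 15 times as large (36.6/2.5 = 14.6), 20% is 8 times, and 11% is over 4 times.

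**The case against.** The strongest reply has several parts.

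1. **A reader might infer that a false benefit would appear in 40–60% of trials with no effect.** That range counts significant harm as well as benefit. In the favourable direction the ceiling is 36.6% for 18 independent outcomes, and non-negative correlation lowers it. This part stands, and the larger range must not be attached to benefit.
2. **Independence is unrealistic.** The article derives BMI from weight, LDL-C from the other lipids, and HOMA-IR and QUICKI by formula. This stands too: the independent figures are upper ends, not best estimates.
3. **A reader might infer that all outcomes have equal rank.** They do not quite. CAP sets the sample size, the stated aim covers only liver enzymes, steatosis and fibrosis, and the metabolic variables are introduced as additional. That is a fair correction, but none of it makes CAP the test of success. The six liver outcomes alone still give 14.1% favourable if independent.
4. **A reader might count three tests per outcome, because three model effects are examined.** The documents do not support this. A time effect is not a comparison of the arms, and with two time points and baseline adjustment the group and interaction terms are closely related. The figures here use one test per outcome.
5. **The recommendation is a discussion sentence, not a formal decision rule.** True, and nothing says that blood pressure alone would trigger it. The text nevertheless leaves the supporting outcome open.
6. **A hierarchy may stand in an analysis plan that is not shown.** It may, and its absence from a condensed article would not by itself be a finding. The point rests on what the article does state: an outcome list without a primary, a level of 0.05, and a recommendation tied to no outcome.

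**Conclusion.** The concern holds in this form: the article designates no primary outcome among about 18, sets 0.05 with no hierarchy or adjustment, and leaves its recommendation unattached to any outcome although the trial is sized on CAP. With no true effect, the chance of at least one favourable significant difference is up to about 37% (independent outcomes), about 20% at a common correlation of 0.5 and about 11% at 0.8. In either direction the first two figures are about 60% and 40%.

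These sizes assume one two-sided group test per outcome, a count of 18, no effect on any outcome, and correlations that are not in the documents. The direction of the conclusion does not depend on the exact correlation: every scenario examined is well above 2.5%.

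**What to change.** By dated amendment before unblinding:

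- In Outcomes and Statistical analysis, name the between-group difference in CAP at 12 weeks, adjusted for baseline, as the single primary outcome, tested at two-sided 0.05. CAP is the natural choice because the sample size is based on it.
- Label all other outcomes secondary or exploratory and report them with 95% confidence intervals. The documents give no basis for a particular testing order among them, so none is proposed.
- In the abstract and the Discussion, tie the recommendation to the CAP result.

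This needs no extra patients or measurements, and the level for CAP stays at 5%. It is more than an edit of wording: the article reports that recruitment started in December 2021, so the change must be dated and made before group results are seen. The price is that no confirmatory claim can come from fibrosis, the enzymes or the metabolic outcomes. The conclusion would also rest on an endpoint whose power cannot be verified from the article, since no SD is given.

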### Ethics and dissemination

This clinical trial study was confirmed by the ethics committee of Tehran University of Medical Sciences (code: IR.TUMS.MEDICINE.REC.1399.1006). Furthermore, it was registered in the Iranian Registry of Clinical Trials (www.irct.ir) at 2021-04-19 (code: IRCT20210201050210N1).

### Trial status

The recruitment started on December 2021.

## Discussion

NAFLD is an important public health issue due to its high global prevalence [31]. It is a clinical syndrome from simple steatosis to cirrhosis, which is associated with insulin resistance, lipo-toxicity, inflammation and obesity [31]. Changes in the composition of gut microbiota, called dysbiosis, are strongly associated with the development and progression of NAFLD [31]. Probiotics play an important role in modulating intestinal bacterial flora and modifying intestinal permeability [31]. Furthermore, the production of short-chain fatty acids by probiotics during fermentation can affect inflammatory, antioxidant, and gene expression pathways, through which they might prevent the progression of liver damage [31]. Previous investigations have reported that consuming probiotic yogurt improves lipid profile, glycemic variables, liver enzyme levels, and steatosis in patients with NAFLD. We are aware of no study examining the effect of probiotic yogurt on liver fibrosis [31]. In addition, earlier studies have mostly applied ultrasound, which is a less accurate method than the fiber scan, to estimate liver fat. Therefore, the aim of our study would be to evaluate the effect of probiotic yogurt consumption on liver enzymes, steatosis and liver fibrosis in patients with NAFLD. Through this investigation and in case of finding an appropriate effect, we would introduce an efficient and cost-effective method to take benefit of probiotics in patients with fatty liver.

Despite several strengths of our study protocol including stratified permuted block randomization and double-blind, placebo-controlled design and conducting the study on newly diagnosed NAFLD patients by fibroscan, some limitations must also be taken into account: We will examine the compliance in this study through collecting dietary intake information by questionnaires. Due to limited funding, we are unable to examine gut microbiota and serum trimethylamine N-oxide (TMAO) as a biomarker for assessment of compliance in this study. We also use probiotic strains available in the food market and did not focus on specific strains that might have different effects. Future studies should examine the effect of foods fortified with specific probiotic strains on steatosis and fibrosis in patients with NAFLD. In addition, another concern might be a limited duration of intervention in this study which would be for 12 weeks. Although one might assume this time period too short for our intervention to affect liver fibrosis, other studies have applied almost the same duration for assessing the effect of intervention of fibrosis among patients with NAFLD.

